#### Inclusion and Exclusion Criteria

Quasi-experimental component: existing children with T1DM aged 10-18 years classified as CGM subusers in substudy 2; primary caregiver consents and child assents.

RCT component: newly diagnosed children with T1DM, aged 10-18 years, eligible for CGM under the national program, who have not yet received CGM. Exclusion: severe psychiatric or cognitive comorbidity precluding informed assent or interview participation.

#### Recruitment

Eligible families will receive a formal invitation letter, information sheet, and consent/assent forms (Multimedia Appendix 6) from RMs, who will explain study objectives and logistics in Arabic and English.

#### Training

A 3-day bespoke training program will be delivered to RMs, diabetes nurses, and administrative staff, covering the OMNIdiasense interface, MI principles, outcome measurement procedures, and ethical considerations.

#### Intervention

Participants in the quasi-experimental arm and the RCT intervention arm will receive 3 MI-guided consultations delivered by trained diabetes nurses at baseline, 3 months, and 6 months (Multimedia Appendix 7). MI sessions will (1) establish rapport, (2) explore pros and cons of CGM use, (3) provide tailored feedback on the OMNIdiasense risk score, (4) elicit imagery of life with and without CGM, (5) review options and develop an adherence plan, and (6) reinforce self-efficacy.

Permitted concomitant care includes routine pediatric diabetes follow-up, school health support, and standard insulin therapy. Discontinuation of OMNIdiasense recommendations will be considered if the family withdraws consent, if a clinical adverse event makes continued sensor wear unsafe, or if the treating clinician determines that a recommendation conflicts with safety. Adherence to the MI fidelity manual will be assessed by audio-recorded session sampling (approximately 10% of sessions per interventionist per quarter), scored using a brief MI fidelity rubric (Multimedia Appendix 8).

#### Outcomes

The primary outcome is the between-group difference in CGM adherence, defined as mean days per week of sensor wear over the 12-month follow-up. The CGM adherence outcome will be measured from pharmacy dispensing records, self-report, and clinical records. Differences between device types will be recorded, and significant findings across different devices will be analyzed.

Key secondary outcomes are change in HbA_1c_, time in range, anthropometric measures (weight and BMI), blood pressure, lipid panel, RFT, LFT, drug/treatment changes, OMNIdiasense risk score change, barriers and facilitators of CGM use, and patient satisfaction (Multimedia Appendix 9). Table 2 shows the full schedule of assessments.

**Table 2 table2:** Schedule of assessments in substudy 3.

Variable		Tool/source	Baseline	3 months	6 months	12 months

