Substudy 3: quasi-experimental single-arm pilot	Quasi-experimental, n=100 existing subusers	Within-person change in adherence and HbA_1c_ after OMNIdiasense-guided MI sessions	Feasibility, acceptability, and effect-size estimates for a future definitive trial.
Substudy 3: pilot RCT^k^ with appropriate reporting standards	Parallel 1:1, n=50 newly diagnosed (25 intervention, 25 control)	Between-group difference in CGM^l^ adherence at 12 months; secondary clinical, behavioral, and satisfaction outcomes	Generates the effect-size, recruitment, retention, and fidelity estimates required for a definitive multicenter trial.

^a^HbA_1c_: hemoglobin A_1c_.

^b^BP: blood pressure.

^c^RFT: renal function test.

^d^LFT: liver function test.

^e^BenCGM: Benefits of Continuous Glucose Monitoring Scale.

^f^BurCGM: Burden of Continuous Glucose Monitoring Scale.

^g^RSQ: Response to Stress Questionnaire.

^h^SEDM: Self-Efficacy for Diabetes Management Scale.

^i^PAID-Peds: Problem Areas in Diabetes-Pediatric version.

^j^PAQ-A: Physical Activity Questionnaire for Adolescents.

^k^RCT: randomized controlled trial.

^l^CGM: continuous glucose monitoring.

CGM distribution in Oman commenced in May 2024 following extensive capacity-building of diabetes clinic staff in 30 health facilities across all governorates. By February 2025, approximately 1500 children with T1DM had received CGMs, recorded centrally in the national Al Shifa health information system.

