#### Sample Size

The pilot RCT sample size was based on the prevalence of optimal CGM use of approximately 50% [25] and a moderate effect (odds ratio 0.53) reported for adolescent CGM use. Using G*Power 3.1 (Heinrich Heine University Düsseldorf), at least 25 participants per arm are required to achieve 80% power at α=.05. The single-arm component (n=100) is powered for paired-sample within-person change in adherence and HbA_1c_.

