**Primary outcome**						
	CGM^a^ adherence (optimizer vs subuser)	OMNIdiasense score	✓	✓	✓	✓
	Sensor-wear days/week	CGM device records	✓	✓	✓	✓
	MI^b^-guided behavior change consultation	Session log	✓		✓	✓

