#### Data Analysis

Analyses will follow the intention-to-treat principle. Descriptive statistics will summarize baseline characteristics. Within-person change in the quasi-experimental arm will be analyzed with paired *t* tests, Wilcoxon signed-rank tests, or generalized estimating equations as appropriate. Between-group differences in the RCT will use *t* tests, chi-square tests, and mixed effects models with random intercepts for repeated measures. Multivariable linear and logistic regressions will explore predictors of adherence change. Missing data will be handled by multiple imputation under a missing-at-random assumption with sensitivity analyses. Prespecified subgroup analyses will examine age band (10-13 vs 14-18 years), sex, governorate (Muscat vs others), and insulin modality (multiple daily injections vs pump); any post hoc subgroup analyses will be flagged as exploratory. The pilot RCT report will follow the CONSORT (Consolidated Standards of Reporting Trials) 2025 extension for pilot and feasibility trials, and the interventional protocol adheres to SPIRIT (Standard Protocol Items: Recommendations for Interventional Trials)-AI 2025 (Multimedia Appendix 10).

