## Discussion

### Anticipated Principal Findings

We anticipate 3 principal findings. First, substudy 1 is expected to show that pediatric CGM uptake in Oman is high in the first 6 months of dispensing, but that a clinically important minority becomes subusers by month 3, with measurable variation across governorates. Second, substudy 2 is expected to confirm prior international findings that perceived benefit and burden of CGM, self-efficacy, and diabetes distress are the strongest psychosocial correlates of optimizer status, with additional Omani-specific contributors emerging from the open-ended responses. Third, substudy 3 is expected to show that OMNIdiasense, used as a decision-support adjunct followed by MI-guided behavioral sessions, is feasible to deliver, acceptable to families and clinicians, and produces a clinically meaningful between-group difference in adherence at 12 months that can power a future definitive trial.

These anticipated findings are framed as testable hypotheses, not foregone conclusions, and all statements throughout the abstract, manuscript, and conclusion have been rechecked to ensure that the strength of language matches the strength of inference that the proposed methodology can support.

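### The pilot RCT's primary outcome is stated on two scales and from conflicting data sources, so the document does not fix which endpoint its result rests on

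*Protocol article*

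**What the plan says.** The protocol article describes the RCT primary outcome in five places.

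- **Substudy 3, Outcomes:** "The primary outcome is the between-group difference in CGM adherence, defined as mean days per week of sensor wear over the 12-month follow-up". The sources given are pharmacy dispensing data, what families report, and the clinical record.
- **Table 2, primary-outcome rows:** the first row is CGM "adherence (optimizer vs subuser" status, with the OMNIdiasense score as its tool. The second is "Sensor-wear days/week", from the CGM device's own records. The third is the motivational-interviewing session log. The first two are scheduled at baseline, 3, 6 and 12 months.
- **Substudy 3, Sample Size:** the calculation starts from a "prevalence of optimal CGM use of approximately 50" per cent and an odds ratio of 0.53, and arrives at 25 per arm for 80% power at α=.05.
- **Table 1, pilot RCT row:** the between-group difference is in CGM "adherence at 12 months; secondary clinical, behavioral, and satisfaction outcomes".
- **Discussion, Anticipated Principal Findings:** the pathway is expected to be one that "produces a clinically meaningful between-group difference in adherence at 12 months".

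The optimizer cut-point, 6 or more days per week, is given in the Abstract and in substudy 2. For RCT between-group comparisons in general, Data Analysis lists t tests, "chi-square tests, and mixed effects models with random intercepts for repeated measures".

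**The concern.** A 12-month average in days per week and a dichotomy at 6 days per week are different endpoints. They answer different questions, need different analyses and give effect sizes that cannot be exchanged. The text names one as primary, tabulates both as primary, and sizes the trial on the other. The sources differ too, and one of them, the OMNIdiasense score, is a predicted probability of becoming a subuser rather than a record of wear.

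Two things are at stake. The Sample Size section presents a powered hypothesis test, so the reader must know which hypothesis it is. Table 1 also says the pilot will supply the effect size for a definitive trial, and an effect size on an undetermined scale cannot do that.

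**Working it through.** **1. The statements side by side**

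| Place | Scale | Time | Source |
|---|---|---|---|
| Outcomes | continuous, days/week | mean over 12 months | dispensing, self-report, clinical records |
| Table 2, row 1 | binary | four visits | OMNIdiasense score |
| Table 2, row 2 | continuous, days/week | four visits | CGM device records |
| Sample Size | binary (prevalence, odds ratio) | not stated | – |
| Table 1 and Discussion | not stated | 12 months | – |

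The scale conflict (Outcomes against Table 2 row 1 and Sample Size) and the source conflict (Outcomes against Table 2) cannot be shorthand. The timing difference may be.

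A hypothetical child shows that the endpoints differ. Wear of 7 days/week for 9 months and then 5 for 3 months averages (9×7 + 3×5)/12 = 6.5 days/week. At 12 months the same child is at 5 days/week and is a subuser.

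**2. The plan's own figure, on its own scale**

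Inputs from Sample Size: p1 = 0.50, OR = 0.53, 80% power, α = .05 (taken as two-sided; sidedness is not stated).

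- p2 = 0.53/(1 + 0.53) = 0.346; difference 0.1536; mean proportion 0.4232.
- n per arm = [1.960×√(2×0.4232×0.5768) + 0.842×√(0.25 + 0.2264)]² / 0.1536² = (1.369 + 0.581)²/0.02359 ≈ 161.2, so 162.
- With continuity correction: 175. One-sided: 127.
- Power at 25 per arm: Φ[(0.1536×√25 − 1.369)/0.690] = Φ(−0.87) = 19% (29% one-sided).
- At 25 per arm, 80% power needs about 50% against 86.5%.

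The stated 25 does not reproduce on the binary scale. That is a separate error; it matters here because the calculation does not belong to the endpoint that Outcomes defines.

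**3. What 25 per arm means on days per week**

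- Detectable difference, normal approximation: (1.960 + 0.842)×√(2/25) = 0.79 SD; exact t test 0.81 SD.
- At 0.5 SD: power about 41%, and 63–64 per arm would be needed.

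The documents give no SD for days per week, so this cannot be turned into days.

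**4. Illustration: free choice among three readings when there is no effect**

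All inputs are assumptions. Setting A: 25 per arm, three follow-up visits, wear = 6 + 1.5×normal deviate clipped to 0–7 (about half at 6 or more), 20,000 runs per row.

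| Between-visit correlation | t test, mean | t test, last visit | uncorrected chi-square, last visit | at least one p<.05 |
|---|---|---|---|---|
| 0.3 | 5.0% | 5.0% | 6.7% | 11.6% |
| 0.5 | 5.1% | 5.1% | 6.6% | 11.0% |
| 0.7 | 5.0% | 4.9% | 6.6% | 10.6% |
| 0.9 | 5.1% | 5.1% | 6.8% | 10.0% |

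Setting B: mean 5.8, between-child SD 1.3, within-child SD 0.9, clipped to 0–7.

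- At least one p<.05: 10.6–11.1% across three runs of 6,000 to 15,000 trials.
- With a continuity-corrected chi-square: 9.0%.
- The two continuous readings only: 7.4%.
- With an assumed true shift of 0.8 day/week, power is 46% (12-month mean), 37% (12-month value) and 33% (binary).

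Three independent tests would give 1 − 0.95³ = 14.3%.

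**The case against.** **Only Outcomes offers a definition.** Table 1 and the Discussion give no scale, and adherence at 12 months can abbreviate the same average. This stands: a reader might count three firmly incompatible definitions, but the text proves a conflict of scale and source, with timing ambiguous.

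**Table 2 is a schedule with loose headings.** Its primary block contains a session log and its secondary block contains demographics. It also contains the days-per-week row, which agrees with Outcomes. This weakens the table as evidence, but the Sample Size section uses the binary scale independently.

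**The list of tests covers all RCT comparisons.** Chi-square tests may be meant for categorical secondary outcomes. Reporting Guidelines and Dissemination says a full statistical analysis plan exists, and mapping tests to endpoints is often left there. This stands: the list alone is not a fault.

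**The result may not be open to choice.** A reader might infer that the primary result can be picked after the data are seen. The unseen analysis plan may already fix it, and the analyst is blinded to allocation. Neither tells a reader of this document which endpoint is primary.

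**Imputation.** A reader might infer that missing-at-random imputation will credit wear to children who stop using CGM. No section says that stopping is coded as missing, and dispensing records could show it as observed non-wear. That claim is unsupported.

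**It is a pilot.** Type I error is not its main purpose. But Sample Size claims 80% power, and Table 1 wants its effect size for a definitive trial.

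**Conclusion.** The point holds as an inconsistency in the primary outcome. Outcomes defines a continuous 12-month mean, Table 2 puts binary status beside it under the same heading with a predictive score as its tool, and Sample Size is argued on the binary scale. The data sources also disagree, and nothing in the document resolves either conflict. This does not depend on any simulation.

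Its size on the plan's own terms: 25 per arm gives 19% two-sided power on the binary scale with the stated inputs, and 80% power on days per week only for a difference of about 0.8 SD.

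The 9–12% chance of a nominally significant result under free choice is an illustration under assumed wear distributions. It should not be read as the trial's type I error. Part of the excess over 5% comes from the uncorrected chi-square test, which alone runs at about 6.6% at this sample size.

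**What to change.** Before substudy 3 recruitment, planned for the fourth quarter of 2026:

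1. Keep the Outcomes definition, mean days per week of sensor wear over 12 months, in every place. Align Table 1, Table 2 and the Discussion with it.
2. Name one data source for it, the same in both arms. The CGM device records already in Table 2 are a candidate. The OMNIdiasense score should not be the source.
3. Tie one primary between-group analysis of that mean to it, reported with a 95% CI. Randomization is simple, so no stratum term is needed.
4. List wear at 12 months and optimizer status as secondary outcomes. Take the session log out of the primary-outcome rows.
5. Restate Sample Size in days per week, with an assumed SD and the difference that 25 per arm can detect (about 0.8 SD for 80% two-sided power).
6. State that weeks with documented non-wear are observed values and are not imputed. How to treat wear stopped for safety or supply reasons is for the sponsor to define.

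The cost is wording changes before recruitment and a less favourable power statement. No new data are needed.

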### Substudy 3: Pilot Evaluation of OMNIdiasense

#### Design

Substudy 3 evaluates the AI-assisted assessment tool OMNIdiasense through 2 parallel components, both fed by an embedded AI model-development workstream described below.

Quasi-experimental single-arm pilot: 100 existing CGM subusers identified in substudy 2 receive OMNIdiasense assessment prior to CGM reintroduction, followed by MI-guided behavioral support delivered by a trained diabetic nurse within the routine pediatrics endocrine clinics.Pilot RCT: 50 newly recruited children with T1DM, randomized 1:1 to (1) intervention, OMNIdiasense assessment plus MI-guided support before CGM initiation or (2) usual care without exposure to the tool. Both arms receive CGM and standard clinical follow-up.

All 150 participants are followed for 12 months, with assessments at baseline, 3, 6, and 12 months. The flow of participants is presented in Figure 1.

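### Device-type differences in sensor wear are to be analysed where significant; a significance condition tends to exaggerate the differences it keeps

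*Protocol article*

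**What the plan says.** Under Outcomes for substudy 3, the primary outcome is a between-group difference in CGM adherence, "defined as mean days per week of sensor wear over the 12-month follow-up". After naming the data sources for that outcome, the same paragraph adds: "Differences between device types will be recorded, and significant findings across different devices will be analyzed". It does not define significant, and it names no test, model or threshold for the device comparison.

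Under Data Analysis for substudy 3, the planned subgroups are listed: "Prespecified subgroup analyses will examine age band (10-13 vs 14-18 years), sex, governorate (Muscat vs others), and insulin modality". Device type is not on the list. The same sentence goes on to say that post hoc subgroup analyses will be flagged as exploratory.

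The sizes involved come from the Design section of substudy 3: an RCT of "50 newly recruited children with T1DM, randomized 1:1 to" two arms, beside a single-arm component of 100 existing subusers. In total, "All 150 participants are followed for 12 months".

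**The concern.** The sentence ties what is analysed to the result obtained. An estimate that is kept because it passed a significance threshold is, on average, further from zero than the truth, and the lower the power, the larger the gap. If there is no true difference, whatever passes is chance alone.

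Two features add to this. Device type is not randomised, so a difference between devices may reflect who received which device. And the status of the comparison is unclear: it is announced in advance under Outcomes but is missing from the prespecified list, so it is neither plainly planned nor plainly post hoc.

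At stake is how far a reader can trust any statement in the results that wear was better on one device than another.

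**Working it through.** **The plan's own figure.** The article gives no figure for the device comparison. The nearest is the RCT sample size: "at least 25 participants per arm are required to achieve 80% power at α=.05", from about 50% optimal use and "a moderate effect (odds ratio 0.53) reported for adolescent CGM use". That figure does not reproduce. An odds ratio of 0.53 against 50% gives p2 = 0.53/1.53 = 0.346. With mean proportion 0.423:

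n = [1.96·√(2·0.423·0.577) + 0.842·√(0.25 + 0.346·0.654)]² / (0.50 − 0.346)² ≈ 161.2, so 162 per arm, two-sided.

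Twenty-five per arm fits a standardised difference of about 0.8. This is a separate matter. It is used here only to show that a two-group comparison at this size has low power unless the difference is large.

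**Inputs for the device comparison.**
- From the article: 50 children in the RCT and 150 in substudy 3; a continuous outcome (mean days per week).
- Assumed: two device types in equal groups, two-sided P<0.05, and true differences d of 0.2, 0.5 and 0.8 SD. The article gives no number of devices, no split and no SD, so results are in SD units.
- The 75-per-group case would need both components pooled. The article does not describe such pooling; the case is shown as the favourable end of the range.

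**Formula.** For groups of size n, SE = √(2/n). With δ = d/SE and c = 1.96:

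- P(significant) = Φ(δ − c) + Φ(−δ − c)
- mean |estimate| given significance = {d[Φ(δ − c) − Φ(−δ − c)] + SE[φ(c − δ) + φ(c + δ)]} / P(significant)

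**Worked case, n = 25, d = 0.2.** SE = √(2/25) = 0.283 and δ = 0.707. An estimate must exceed 1.96 × 0.283 = 0.55 SD to be significant, which is already 2.8 times the true value.

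- P(significant) = 0.1051 + 0.0038 = 0.109
- mean kept estimate = [0.2 × (0.1051 − 0.0038) + 0.283 × (0.1820 + 0.0114)] / 0.109 ≈ 0.69 SD, or 3.4 times the truth

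**All cases, by simulated t test (200,000 runs each).**

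| Per group | True d (SD) | P(significant) | Mean kept estimate (SD) | Ratio to truth |
|---|---|---|---|---|
| 25 | 0.2 | 0.107 | 0.68 | 3.40 |
| 25 | 0.5 | 0.410 | 0.76 | 1.53 |
| 25 | 0.8 | 0.790 | 0.90 | 1.13 |
| 75 | 0.2 | 0.230 | 0.41 | 2.07 |
| 75 | 0.5 | 0.860 | 0.54 | 1.08 |
| 75 | 0.8 | 0.998 | 0.80 | 1.00 |

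With no true difference, 5% of comparisons pass. Those that pass show a mean absolute difference of 0.65 SD with 25 per group and 0.38 SD with 75.

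Unequal splits are worse: at 40 and 10 children with d = 0.2, the ratio is 4.20.

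**More than two devices.** If all pairs were tested at 0.05 without correction in 150 children, the simulated chance of at least one false positive is about 5%, 12% and 20% for two, three and four device types.

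**The case against.** The strongest reply is that the sentence does not say what a critic may hear in it.

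- **Suppression.** A reader might infer that non-significant device differences will be left out of the report. The text does not support that. It has no word such as only, says nothing about reporting, and states that differences will be recorded.
- **Meaning of significant.** It could mean notable; taken literally, a P value cannot be known before an analysis is done. This stands as an ambiguity. It does not remove the problem, because a looser meaning still lets the result decide what is pursued, with no threshold.
- **Exploratory label.** The Data Analysis section does flag post hoc subgroup analyses as exploratory, and Strengths and Limitations says the pilot effect sizes need confirmation. Both limit the weight of a device finding. Neither undoes selection on the result, and it is unclear whether a comparison announced in advance counts as post hoc.
- **Detail left to the analysis plan.** The article says a full statistical analysis plan exists. The test, the model and any multiplicity rule belong there, and their absence here is no fault. The significance condition is different, because the article states it.
- **Size.** A reader might infer that every device difference will be exaggerated or false. That is too strong. The bias is an average, and it nearly vanishes when true differences are large.
- **Effect on the trial result.** A reader might infer that the arm comparison is compromised. It is not filtered on device significance. It is also tempting to ask for the RCT analysis to be adjusted for device. But RCT children have not yet received CGM at entry and the intervention comes before initiation, so the device is dispensed after randomisation and could be influenced by the arm.

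**Conclusion.** The point holds in a limited form. On its natural reading, the sentence makes significance the condition for pursuing a device comparison on the adherence outcome, for a non-randomised factor outside the prespecified subgroup list. Estimates kept on that condition will tend to be too large and may be false.

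Within the RCT's 50 children, the exaggeration runs from about 3.4-fold to 1.1-fold as the true difference goes from 0.2 to 0.8 SD. If all 150 children were pooled, it would run from about 2.1-fold to none. A split of the 100 single-arm children into two equal groups of 50 would fall between. These figures rest on two equal device groups and a P<0.05 filter, neither of which the article states.

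This is an ancillary comparison in a pilot. The primary between-arm analysis is untouched, and the priority is low.

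**What to change.** Replace the sentence under Outcomes with:

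*Sensor wear will be summarised by device type with 95% CIs for all devices, whatever the P value, within each substudy 3 component, as an exploratory analysis.*

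This removes the significance condition, settles the status of the comparison, and keeps existing subusers and newly diagnosed children apart. Do not add a device-adjusted sensitivity model for the RCT.

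The cost is one sentence and a few more rows of output. Device differences are already to be recorded, so no new data are needed and the design does not change.

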#### Expected Outcomes

Primary outcomes of substudy 1 are (1) the population-level prevalence of CGM optimizer status at ≥3 months and (2) the pre-post change in HbA_1c_. Secondary outcomes are pre-post changes in weight, BMI, BMI *z* score, systolic and diastolic blood pressure, lipid panel, renal function test (RFT), and liver function test (LFT); regional variation across governorates; and identification of routinely captured clinical predictors of optimal use that will be carried forward to the AI model in substudy 3.

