**Secondary outcomes**						
	Demographic characteristics	Study questionnaire	✓			
	Medical history of T1DM^c^	Study questionnaire	✓			
	Family history of diabetes	Study questionnaire	✓			
	Comorbidities	Study questionnaire	✓			
	Drug/treatment history	Health records	✓		✓	✓
	Anthropometrics (weight, BMI)	Health records	✓		✓	✓
	Blood pressure	Health records	✓		✓	✓
	Cholesterol, RFT^d^, LFT^e^	Health records	✓		✓	✓
	HbA_1c_^f^	Health records	✓		✓	✓
	Barriers and facilitators	Open-ended interview	✓		✓	✓
	Patient satisfaction	Satisfaction questionnaire			✓	✓
	Staff satisfaction (exit survey)	Satisfaction questionnaire				✓

^a^CGM: continuous glucose monitoring.

^b^MI: motivational interviewing.

^c^T1DM: type 1 diabetes mellitus.

^d^RFT: renal function test.

^e^LFT: liver function test.

^f^HbA_1c_: hemoglobin A_1c_.

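### Substudy 3 lists only raw weight and BMI change over 12 months in 10-18-year-olds; in the uncontrolled single arm, normal growth can pass for change after the intervention

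*Protocol article*

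**What the plan says.** Protocol article, Substudy 3, Outcomes: the key secondary outcomes, expressed as change, include "anthropometric measures (weight and BMI"), followed by blood pressure, laboratory and other items. Table 2, the schedule of assessments, has the row "Anthropometrics (weight, BMI"), taken from health records at baseline, 6 and 12 months. Neither place mentions a z score, a centile or any other standardisation for age and sex.

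Substudy 1, Expected Outcomes, goes further and lists "pre-post changes in weight, BMI, BMI *z* score". It keeps the raw measures, adds the z score, and names no growth reference.

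Both components of substudy 3 enrol growing children. The single arm takes "existing children with T1DM aged 10-18 years classified as CGM subusers in substudy 2" and the RCT takes "newly diagnosed children with T1DM, aged 10-18 years" (Inclusion and Exclusion Criteria). On follow-up, the Design section says: "All 150 participants are followed for 12 months". Under Data Analysis, the single arm of 100 is analysed as within-person change by paired t test, Wilcoxon signed-rank test or generalized estimating equations. The RCT of 25 per arm is analysed as a between-group difference.

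**The concern.** Raw weight and BMI are expected to rise over a year in many children of this age, whatever care they receive. A within-person test asks whether the mean change is zero. For a raw measure in growing children, zero is not the value expected when the intervention does nothing. A rise in the single arm would then mix growth with any effect of the tool, the motivational interviewing sessions or renewed CGM use, and there is no control group to separate them.

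The risk of misreading is practical. The tool's recommendations cover meal timing and physical activity (Personalization and Feedback Mechanism), so a weight or BMI change could easily be credited to the intervention or held against it. The planned subgroups by age band (10-13 vs 14-18 years) and by sex have the same problem in the single arm, because raw change could differ between these strata through growth alone.

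The programme names the standardised measure in substudy 1, where the minimum window is 3 months, and leaves it out of substudy 3, where follow-up is a full year.

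**Working it through.** The protocol states no figure that depends on the anthropometric scale, so there is nothing to reproduce. The check asks how often growth alone would give a nominally significant result.

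**Inputs from the protocol:** n=100 in the single arm, within-person analysis, 25 per arm in the RCT, and α=.05 (stated for the RCT sample size; taken as two-sided here).

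**Assumed inputs (not in the documents):** 12-month mean BMI drift of 0.2 to 0.8 kg/m² with SD of change 1.0 to 2.0; mean weight drift of 1 to 2 kg with SD of change 3 to 5 kg; all 100 children analysed at 12 months; no intervention effect.

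**Single arm, paired t test.** The noncentrality is (drift / SD) × √100. With c the 97.5% point of t on 99 degrees of freedom, P(p<0.05) = 1 − F(c) + F(−c), where F is the noncentral t distribution. Two worked cells:

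- drift 0.2, SD 2.0: 0.2/2.0 × 10 = 1.0, giving 17%
- drift 0.4, SD 1.0: 0.4/1.0 × 10 = 4.0, giving 98%

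| Assumed BMI drift (kg/m²) | SD 1.0 | SD 1.5 | SD 2.0 |
|---|---|---|---|
| 0 | 5% | 5% | 5% |
| 0.2 | 51% | 26% | 17% |
| 0.4 | 98% | 75% | 51% |
| 0.6 | ~100% | 98% | 84% |
| 0.8 | ~100% | ~100% | 98% |

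For weight, a drift of 1 kg gives 91%, 70% and 51% at SD 3, 4 and 5 kg. A drift of 2 kg gives 98% or more at all three.

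As a rule of thumb, the drift that gives an 80% chance of p<0.05 is (1.960 + 0.842)/√100 = 0.28 SD.

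**RCT, two-sample t test, 25 per arm, 20,000 simulated trials.** With the same mean weight gain in both arms (0, 2, 4 or 5 kg, SD 4 kg), the rejection rate is 4.9% to 5.1%. If each child has an even chance of gaining 5 kg on average (younger) or 1 kg (older), the rate is 5.0%. The spread of growth adds a variance of ((5 − 1)/2)² = 4, so the SD of change rises from √16 = 4 to √20 = 4.47, a ratio of 1.12. The test keeps its level and loses some precision.

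**With a z score.** If the growth reference describes these children, expected drift under normal growth is 0. The single-arm rate then returns to the 5% of the first row.

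**The case against.** The strongest reply is that scaling an outcome is a derivation detail. The protocol refers to a full statistical analysis plan that is not shown, a z score is calculated and so need not appear in a schedule of assessments, and nothing says z scores will not be used. Part of this stands: the plan could still be carried out well. But this article does specify anthropometrics down to the z score in substudy 1, and the two lists in substudy 3 then name weight and BMI only. As written, the outcome is raw change.

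A second reply is that Table 1 gives adherence and HbA1c as the single-arm outputs, that the arm is described as powered for those two only, and that the analysis section is generic. This is correct, and no sentence commits to a paired test of BMI in particular. Still, the secondary outcome list and Table 2 apply to substudy 3 without exempting the single arm, and within-person change is the only analysis given for it.

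Three stronger readings are tempting, and the documents do not support them:

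- A reader might infer that growth also biases the RCT result. It does not: randomisation balances growth in expectation. Chance imbalance in age or sex at 25 per arm is covered by the nominal error rate and costs only precision.
- A reader might infer that substudy 1 has replaced raw measures with the z score. It lists all three.
- A reader might infer that growth is bound to give p<0.05 in the single arm. That depends on drift and SD values the documents do not give; at the low end of the range the chance is about 17%.

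**Conclusion.** The point holds for the uncontrolled single arm, 100 of the 150 participants in substudy 3. There, raw weight and BMI change confounds normal growth with change after the intervention. Over the assumed range, the chance of a nominally significant BMI change with no intervention effect is about 17% to nearly 100%, against 5% for a measure with no expected drift. That range rests on assumed growth and SD values and on complete 12-month data; the direction of the problem needs only that mean raw BMI or weight rises with age in this group.

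In the RCT the between-group comparison is valid on the raw scale, with an SD about 12% larger in the age-dependent example. These are secondary outcomes in a pilot, and neither the primary adherence outcome nor any sample-size figure depends on them. The change is a free improvement.

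**What to change.** In Substudy 3, Outcomes, and in Table 2, add BMI z score (and weight z score if wanted), standardised for age and sex, as the measure for inference on anthropometric change. Name one growth reference and use it in substudies 1 and 3, since substudy 1 does not yet name one. Keep raw weight and BMI as descriptive values, and state that their change in the single arm is not to be interpreted as an intervention effect. The z score removes expected growth only; the single arm still has no control, so its z-score change should also be reported with caution.

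The cost is wording. Weight and BMI are already scheduled, and age and sex are already needed for the planned subgroups. Substudy 3 recruitment is planned for the fourth quarter of 2026, so the change can be made before enrolment.
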